**Fig 1 pone.0270766.g001:**
[figure not shown]
SPIRIT statement. Description of the study steps: 6MWT: 6 Meter Walk Test; STST: Sit-To-Stand Test; ACT: Arm Curl Test; GSES-12: General Self Efficacy Scale; DASS-21: Depression, Anxiety and Stress Scale; MSPSS: Multidimensional Scale of Perceived Social Support; SF-12: Self-reported Quality of Life Questionnaire-version 2; BRSQ-36: Behavioral Regulation in Sport Questionnaire.

**Fig 2 pone.0270766.g002:**
[figure not shown]
Flow chart.

### Setting and population

This study will be conducted at the Hospital Real y Provincial Nuestra Señora de Gracia (HPNSG) and the Hospital Royo Villanova (HRV), both in Zaragoza (Spain). Recruitment will be carried out at post-COVID-19 rehabilitation unit. Participants will be patients who had been infected by the COVID-19 and have been discharged from the hospital.

#### Eligibility criteria

All potential participants will be informed before and will have to give their consent to participate in the study. The inclusion criteria will be: 1) post-COVID-19 patients discharged after more than 5 days hospitalized; 2) aged 18 to 75 years; 3) independent standing with or without technical aids; and 4) present a degree of fatigue ≥4 points in the FSS. The exclusion criteria will be: 1) having any other central and/or peripheral neurological disorders; 2) a previous history of rheumatic pathology or acute musculoskeletal injury; 3) patients with severe hypoxemia, defined as having a SaO2 less than 90% or a respiratory rate ≥30; 4) having any cardiac comorbidities or signs of cardiovascular instability as uncontrolled arrythmia, blood pressure and/or effort angina; 5) having any other contraindicated pathology for moderate-intensity aerobic or strength exercise; 6) a score ≤24 evaluated with the validated Spanish version of Mini-mental State Examination (MMSE-MEC) [33]; 7) no access to internet; and 8) to be unable to follow oral and written instructions in the Spanish language.

#### Allocation and blinding

Participants will be assigned to the intervention or the control group through the software www.randomizer.org by an independent researcher, not involved in the treatment or evaluation, conducted at 1:1 ratio, giving each participant an identification code (IC) to guarantee their anonymity. The envelopes will be securely stored and will be opened in sequence to reveal group allocation.

Both, participants, and main researchers, will be masked to the randomization sequence. The evaluator will be unaware of the allocation and the intervention researcher will not participate in the evaluations.

### Procedure

At the time of hospital discharge all potential participants will receive the study information with a telephone number to contact. Those who agree to participate will call to the information number provided in the information sheet. One of the researchers of the study will ensure that the patient meets the inclusion and exclusion criteria and will schedule the patient for the baseline and pre-intervention assessment. In the first meeting with the researcher, the patient will be asked to sign the informed consent form.

All assessments will be always performed at the same time and place in the hospital to maximally preserve the participant conditions. Each assessment will last about 60 min. This evaluation shall be carried out according to the same procedure previously trained.

Once the baseline and pre-intervention evaluation is completed, a second researcher will assign each patient to the ATG or BRG according to the 1:1 randomization previously done with a web page (www.randomizer.org). This same researcher will help the ATG patients to install the telerehabilitation platform in the mobile (through an app) or will explain the home booklet-based program to the BRG patients. The intervention will be prescribed considering the starting level of the program which will depend on the pre-intervention FSS score.

Every two weeks during the intervention, all patients will receive a control call from the second researcher to ask them about possible incidents and decide if the patient must progress to the next exercise phase based on the intensity of fatigue perceived by each patient. Three- and six- months after the intervention, patients will receive a follow-up call to analyze the level of fatigue (FSS), the functional status (PCFS), the quality of life (SF-12) and the psychosocial factors (GSES-12, DASS-21, BRSQ-36, MSPSS) (Figs 1 and 2).

### Intervention

The ATG and BRG will receive the same therapeutic exercise and education program. It has been designed following the recommendations of the Spanish physiotherapy associations, the Spanish Society of Pneumology and Thoracic Surgery (SEPAR) and the American Thoracic Society (ATS) [34–36]. The program will be performed for 12 weeks (three sessions/week). The therapeutic exercise program will include aerobic, strength and lung capacity exercises [37]. It will be composed of three levels of difficulty with different exercises in each one, except for the pulmonary exercises (S1 Appendix). The first level will include patients with a score equal to or greater than 6 on the FSS, the second level will include those with a score between 5–5.99 and the third one will include those patients with a score between 4–4.99. Every patient, regardless of their initial level, will start with 10 minutes of the proposed aerobic exercise and 3 sets of strength exercises doing as many repetitions as the patient can. The lung capacity exercises will be the same throughout the entire intervention and will be performed in 2 sets of 10 repetitions with a fatigue level below 3 on the Borg Scale.

The intensity will be measured with the modified Borg Scale. All participants will start for the first two weeks with a fatigue intensity between 3 and 4 and, after 2 weeks, the intensity will be increasing to levels between 5–7 level. Patients will progress every two weeks according to the information provided during the control calls. The appearance of symptoms such as chest pain, lot of coughing, high fatigue, fever, dizziness, or any others deemed relevant, will be taken into account not to progress with the exercises.

The therapeutic education program will be available to all participants during the 12-week intervention. It will consist of 3 blocks of health advice. The first block will focus on how to prevent reinfection by COVID-19 though hygienic recommendations. The second block will focus on how to plan daily life when the patient is at home for a longer period and the third block will focus on psychological advice to reduce levels of anxiety and stress during the recovery period.

#### Intervention group

The ATG will perform the program through a telerehabilitation platform which is accessible via www.hefora.net or with an app mobile that will be installed in the patients´ mobile (HEFORA, Fisio Consultores, Zaragoza, Spain). Therapeutic exercises will be presented in the form of an explanatory video with a specific description (Fig 3). The platform allows the physical therapist to customize the number of sets, repetitions, speed, and observations for each patient. The therapeutic education recommendations will be presented through animated educational videos, explaining to the patients the health and emotional tips to improve their quality of life after COVID-19.

**Fig 3 pone.0270766.g003:**
[figure not shown]
HEFORA interface.

#### Control group

The BRG will perform the same therapeutic exercise and education program than the ATG but through a booklet-based rehabilitation, which will include key pictures and descriptions for every exercise of each level. In addition, patients in the BRG will receive the same therapeutic education recommendations that in the ATG but in text format.

### Outcome measures

#### Primary outcome: Fatigue

The primary outcome measure will be the fatigue, measured with the Fatigue Severity Scale (FSS). The FSS is a self-reported scale that allows assessing the severity of fatigue as a sense of physical tiredness, muscle weakness and lack of energy [38–40]. It is composed of 9 items with scores ranging from 1 = strongly disagree to 7 = strongly agree. The higher the number, the greater the severity of fatigue. The most common cut-off point is a mean score of 4 point, considering equal or more than 4 as severe fatigue [38, 41–45]. Three levels of severity will be considered: 4 = borderline fatigue; 5 = high fatigue; 6–7 = very high fatigue [44]. It has been shown to be reliable [38].

#### Secondary outcomes: Functional status, psychosocial factors, quality of live and feasibility

*Functional status*. It will be measured using the main recommended test for post-COVID-19 patients [46].

Aerobic capacity
6MWT is a sub-maximal exercise test used and recommended to assess the maximum distance possible for six minutes, in a 30-meter corridor, allowing the patient to rest as needed. It has been shown to be reliable [47–49]. The distance covered by each participant will be compared with the estimated distance for their gender, weight, and age according to the Troosters equation [50–52].Strength
30” STST is part of the Senior Fitness Test (SFT) designed by Rikli and Jones and it will be used as a stand-alone test, especially to assess weakness in respiratory patients who have passed COVID-19 [53–55]. It has been shown to be reliable in adults with asthma or pulmonary hypertension [53, 56–58]. This test will be performed with a chair, with the patient´s feet resting on the floor and the arms crossed on the chest. Once in this position, the patients will sit down and stand up to the starting position as many times as possible within 30 seconds [59].30” ACT is part of the SFT and is also used as a stand-alone test to assess strength. It has been shown to be reliable [53, 60, 61] in deconditioned patients and in the elderly population. From a sitting position, the patient is asked to do as many elbow flexion-extension movements as possible with his/her dominant limb during 30 seconds with a two kg weight. The higher number of repetitions the better strength [53, 59].Functional Status post-COVID
PCFS is a scale specially designed and that has been shown to be reliable to assess the functional status of patients who have gone through COVID-19 at discharge [50, 62–64]. It consists of four levels of post-COVID-19 functional limitations been: D = death; 0 = no limitation; 1 = no significant functional limitation; 2 = mild functional limitation; 3 = moderate functional limitation; 4 = severe functional limitation. This scale can be administered by telephone or self-administered [12].

*Psychosocial factors*.

Self-efficacy will be measured with the General Self-Efficacy Scale (GSES-12), which is an abbreviated scale developed by Bosscher and Smit [65]. It is composed of 10 items scored on a Likert scale from 1 = never happens to me, to 5 = always happens to me. It has been shown to be reliable [66]. The higher the score, the greater the perceived self-efficacy [65, 67–70].The level of depression, anxiety and stress will be measured with the Depression, Anxiety, and Stress Scale (DASS-21), which is a set of 3 self-reported questionnaires designed to measure the negative emotional states of depression, anxiety, and stress. Each of these DASS subscales contains 7 Likert-type items with a score from 0 = did not apply to me, to 3 = applied to me very much or most of the time. The total score for the global scale score ranges from 0 to 21 points. The higher scores indicate higher levels of stress, depression, and anxiety [71–73]. The DASS-21 has been shown to be reliable [74, 75].The Behavioral Regulation in Sport Questionnaire (BRSQ-36) will be used to measure the motivation to practice physical activity. It has been shown to be reliable [76, 77]. The BRSQ-36 is composed of 36 items, and it is divided in three main domains: extrinsic motivation: integrated regulation (items 5,14,23,32), identified regulation (items 6,15,24,33), introjected regulation (items 7,16,25,34) and external regulation (items 8,17,26,35); intrinsic motivation: knowledge (items 2,11,20,29), performance (items 4,13,22,31), stimulation (items 3,12,21,30) and general (items 1,10,19,28) and 3); and amotivation (items 9,18,27,36). Its items are valued using a Likert scale that ranges from 1 = not at all true, to 7 = very true. A higher total score on each of the factors indicates a higher dominance of that motivational factor [78].The perceived social support will be measured with the Multidimensional Scale of Perceived Social Support (MSPSS) [79]. It is considered a priority scale to be applied in people who are in the process of recovery. It has been translated and validated in different languages [80]. It measures social support in 3 domains, family, friends, and significant others. It has a three factors structure with each subscale comprising four items addressing practical help. Emotional support, availability to discuss problems and help in decision making. The version used will consist of 12 items that are answered using a Likert scale that ranges from 1 = totally disagree, to 7 = totally agree. Total scores from 12–14 indicate low social support, scores from 49 to 68 indicate moderate social support, and scores from 69 to 84 indicate high social support [81, 82].

*Quality of life*. It will be measured with the Self-Reported Quality of Life questionnaire, version 2 (SF-12). The SF-12 is a shortened version of the SF-36 conducted in 2002. It consists of 12 questions covering 8 dimensions which are grouped into two components, physical and mental. The scores for each item are different and range from 1–2 to 1–6. The overall score ranges from 0 to 100 considering both components. Its interpretation is based on the reference values for the Spanish population, indicating higher scores a higher self-perceived quality of life [83–85]. The version 2 of SF-12 has been shown to be reliable in a student population during COVID-19 [86, 87].

*Feasibility*. It will be measured by the recruitment and adherence rate, the report of satisfaction and the number of incidences. It will be reported with a diary in the telerehabilitation platform or in a diary in the booklet [88, 89].

Adherence is the degree to which a person’s behavior, with respect to taking medication or lifestyle change recommendations, is in accordance with the prescriptions of the healthcare professional. It will be recorded in the activity logs of the brochure or through the platform questionnaire and will be coded by means of a Likert scale, with 0 = if do not has performed the exercises, 1 = if has have carried out some exercises, 2 = if has performed all recommended exercise, and 3 = if they have carried out more additional activity. Additional physical activity will be understood as voluntary physical activity that exceeds the recommended daily activity. A high adherence will be considered when the participant performs at least the 80% of the sessions, and they have done all recommended exercised or more. Non-adhesion will be considered to perform less than 20% of the sessions [90, 91].Recruitment rate, will be calculated based on the percentage of the sample size recruited.Satisfaction with the pilot process will be recorded with a predetermined questionnaire on a Likert scale, from 0 = very dissatisfied, to 4 = very satisfied [92–94]. Participants will evaluate the overall aspects, the brochure, the platform, the attention received, and the exercises given.Incidents will be assessed during the control calls: 0 = no incidences; 1 = some incidence but it has been solved; 2 = incidences that makes it impossible to follow up that period.

All the clinical outcomes (FSS, PCFS, GSES-12, DASS-21, BRSQ-36, MSPSS, SF-12) will be measured at pre-intervention, post-intervention and at three- and six-months follow-up. The functional status outcomes (6MWT, 30” ACT and 30” STST) only will be measured pre- and post-intervention. Regarding the feasibility outcomes, incidences and adherence will be collected during the control calls every two weeks. Satisfaction will be measured in the post-intervention evaluation. The timeline is shown in Fig 4.

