## Methods

### Study design

This protocol will be a pilot and feasibility study with a single-blind randomized clinical trial design. The trial has been designed according to the Standard Protocol Items: Recommendations for Interventional Trials (SPIRIT) and will compare two parallel interventions: an intervention group (asynchronous telerehabilitation group, (ATG)) and a control group (booklet-based rehabilitation group, (BRG)). The duration of the study will be 12 months, with 12 weeks of intervention and two follow-ups at three- and six-months post-intervention. Figs 1 and 2 illustrate the pilot trial design. The study protocol has been approved by the Ethics Committee of Aragón (reference number: PI21/019, current protocol version date April 04, 2021). The protocol has been registered at clinialtrials.gov (NCT04794036).

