#### Sample size calculation

A sample size of 50 subjects will be required, 20 in each group, plus 10 in anticipation of future losses according to the recommendations for RCT pilot studies [95, 96].

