## Discussion

This protocol describes a pilot and feasibility study to analyze the efficacy of an exercise and education therapeutic program using asynchronous telerehabilitation for post-COVID-19 patients. The aim of the pilot study will be to analyze if there are improvements in the participants´ level of fatigue and if these changes are maintained in the short (3 months) and medium term (6 months) and compare it with traditional home rehabilitation using a booklet. The secondary aim will be to analyze the feasibility of this pilot study.

Telerehabilitation is well accepted in terms of overall user experience, adherence, and satisfaction [94]. So, it represents a great opportunity for the treatment and monitoring of long-term patients. Currently, the large increase of COVID-19 cases during 2020 and 2021 has made telerehabilitation-based consultation a viable and reliable option in several pathologies. Scientific evidence shows how telerehabilitation is already effective in post-COVID-19 patients, as reported in the systematic review of da Silva et al. [97] where it was found that a physical programme using telerehabilitation can improve functional capacity, dyspnea and quality of life. Similarly, Dalbosco-Salas et al. [98], found that a group of post-COVID-19 patients undergo remote rehabilitation using synchronous telerehabilitation, achieved improvements in physical condition and quality of life. Although their model is on-line and there is no control group, the study shows positive results for post-COVID-19 patients in lower limb strength and quality of life. Furthermore, in most of the studies carried out in the acute and post-COVID-19 patients, the control group does not receive treatment.

Moreover, telerehabilitation has also shown to be effective in many other different conditions such as musculoskeletal pain, chronic obstructive pulmonary disease (COPD) or cardiovascular disease [99]. The study of Lewis et al. [100] showed that telerehabilitation is effective in COPD patients on multiple variables such as lower limb strength, fatigue, dyspnea, and anxiety, including improvements also in patient engagement and exercise progression. Similar results were obtained by Batalik et al. [101], who performed a study with asynchronous telerehabilitation in cardiac patients and showed also to be effective to improve the aerobic capacity assessed with the 200 meter fast-walk test.

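### The recruitment rate is a percentage of the planned 50, so it shows a shortfall but not uptake or pace once the target is met

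*Protocol article*

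**What the plan says.** The Study design section of the protocol article describes the trial in these words: "This protocol will be a pilot and feasibility study with a single-blind randomized clinical trial design". The Discussion ranks the aims: "The secondary aim will be to analyze the feasibility of this pilot study".

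The section on secondary outcomes says of feasibility: "It will be measured by the recruitment and adherence rate, the report of satisfaction and the number of incidences". It then defines each component. For recruitment the whole definition is: "Recruitment rate, will be calculated based on the percentage of the sample size recruited". The sample size section supplies the only figure to which this can refer: "A sample size of 50 subjects will be required, 20 in each group, plus 10 in anticipation of future losses".

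The Procedure section describes how patients come in. First, "At the time of hospital discharge all potential participants will receive the study information with a telephone number to contact". Then, "Those who agree to participate will call to the information number provided in the information sheet". A researcher checks the inclusion and exclusion criteria after that call. Consent, baseline assessment and allocation follow.

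**The concern.** A feasibility study usually looks at recruitment to learn two things for a larger trial: what share of the patients who could be reached will enter, and how fast they enter. The definition contains neither the number of patients reached nor any unit of time. Its denominator is fixed in advance by the design, so reaching the target fixes the result.

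The opt-in route gives this some weight. Patients receive a sheet at discharge and must telephone on their own initiative. Losses between sheet and call may be a main uncertainty for a larger trial, and they affect how far enrolled patients represent those discharged. The defined rate takes no account of that step. Two pilots with very different prospects of scaling up would report the same figure.

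**Working it through.** **Inputs from the article.** Planned sample: 20 per group, two groups, plus 10 for losses (sample size section). Definition of the rate: secondary outcomes, feasibility. Study duration: 12 months, with 12 weeks of intervention and follow-up to six months afterwards (Study design). Two hospitals (Setting and population). The article gives neither the number of patients informed nor a separate recruitment period.

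**Step 1: the target.** 2 × 20 + 10 = 50, as the article states.

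**Step 2: what the defined rate can show.** Rate = recruited / 50.

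- 25 recruited: 25/50 = 50%
- 40 recruited: 40/50 = 80%
- 45 recruited: 45/50 = 90%
- 50 recruited: 50/50 = 100%

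The rate registers under-recruitment. It has no further information to give once 50 are in.

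**Step 3: what it leaves out on uptake.** The numbers informed below are assumptions, chosen to span a wide range. Proportion recruited p = 50/n. The 95% interval is Wilson's, with z = 1.96: [p + z²/(2n) ± z·√(p(1−p)/n + z²/(4n²))] / (1 + z²/n). For n = 200 this is [0.25 + 0.0096 ± 1.96 × 0.0310] / 1.0192, or 19.5% to 31.4%.

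| Informed (assumed) | Recruited | Recruited / informed (95% CI) | Rate as defined |
|---|---|---|---|
| 60 | 50 | 83.3% (72.0 to 90.7) | 100% |
| 100 | 50 | 50.0% (40.4 to 59.6) | 100% |
| 200 | 50 | 25.0% (19.5 to 31.4) | 100% |
| 500 | 50 | 10.0% (7.7 to 12.9) | 100% |

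**Step 4: what recruited / informed itself mixes.** Eligibility is checked only after the patient telephones, so the overall ratio is a product:

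randomised / informed = (callers / informed) × (eligible / callers) × (randomised / eligible).

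A low product could come from patients not calling, from callers failing the entry criteria, or from eligible patients declining. These mean different things for a larger trial. The percentages in Step 3 are therefore overall yield, not willingness to take part.

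**Step 5: pace.** The formula has no time term. The stated duration sets some limit: "The duration of the study will be 12 months, with 12 weeks of intervention and two follow-ups at three- and six-months post-intervention". If the 12 months cover everything, the time left for enrolment is 12 − 12/(52/12) − 6 = 12 − 2.77 − 6 = 3.2 months. Filling the trial in that time would need 50/3.23 = 15.5 patients a month, or about 7.7 per hospital. This window is an inference, because the article does not state one. If enrolment instead took 6 or 12 months, accrual would be 50/6 = 8.3 or 50/12 = 4.2 a month, and the defined rate would still be 100% once 50 were in.

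**The case against.** **The measure has some value.** Whether two hospitals can reach 50 at all is a feasibility question, and the percentage of target answers it. A reader might infer that the rate says nothing about feasibility. Step 2 shows otherwise: it reports any shortfall.

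**The duration limits the time.** A reader might picture a trial that takes two years to fill and still scores 100%. A study stated to last 12 months does not allow for that, so the example should not be used. Against a fixed window, percentage of target would also carry some information on pace. But no recruitment window is stated and none enters the definition, so this help is only partial.

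**Recruitment is one of four feasibility measures.** Adherence, satisfaction and incidents are defined separately, adherence with explicit thresholds. Feasibility is the secondary aim, and no progression decision in the article depends on the recruitment rate. It would go too far to infer that the study cannot tell a feasible main trial from an infeasible one.

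**Self-selection is not concealed.** The opt-in route is openly described. The flow chart (Fig 2) is not available here and may count informed and screened patients. A full protocol may provide for a screening log, and its absence from an article is no defect. None of this changes the definition that the article does state.

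**The sentence is loosely worded.** A different intended meaning, such as a percentage of those approached, cannot be excluded, but the text does not say it.

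All five objections narrow the point. None gives the defined rate a denominator of patients or a unit of time.

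**Conclusion.** The point holds in limited form. As worded, the recruitment rate measures completion of the target. It is informative below 50 recruits and constant at 100% once 50 are reached, so in a trial that fills it measures neither uptake nor pace. That defeats part of the stated feasibility aim. It does not touch the fatigue comparison or the other three feasibility measures.

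The conclusion rests on reading the sample size as the planned 50, the only one in the article. The size of the problem in this trial is unknown, because the number informed is not given. The spread from 83% to 10% is an illustration with assumed inputs, and Step 4 explains why even those figures are not pure uptake. The correction is worth making because it is cheap and because the counts may be impossible to recover later.

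**What to change.** Keep the percentage of target if wanted, described as completion of the planned sample. Define recruitment by three successive proportions that follow the order of the Procedure section, each with a 95% confidence interval:

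- callers / patients informed at discharge
- eligible / callers
- randomised / eligible

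Add the number randomised per month per hospital over the actual recruitment window, with its start and end dates. A ratio of eligible to informed should not be used: patients who do not call are never screened, so it would mix non-response with ineligibility.

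The source would be a log of information sheets issued, calls received, exclusions and refusals. The diaries that the article names for reporting feasibility belong to enrolled patients and cannot supply these counts.

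The cost is minor clerical work at two hospitals. The log must start with recruitment, since uncounted sheets and calls may not be recoverable. If recruitment has already begun without one, report the proportions from the date the log starts and say so.
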